## Randomization and blinding

8

We plan to use the complete randomization function of SAS 9.13 statistical software (SAS Institute, Cary, NC) to create a table of random numbers that will be printed out and placed in a light-proof envelope and managed by a third party (not the investigators). Under a double-blind design, BYZJ granules and BYZJ simulated granules will be provided to patients in the BYZJ and placebo groups, respectively. Both formulations will be provided by the Dongzhimen Hospital pharmacy and labeled as constipation No. 1 and 2, respectively. In order to ensure blinding, both formulations will have identical packaging. The third party will be responsible for the implementation of blinding and its removal after the trial.

In the event of a potential Suspected Unexpected Serious Adverse Reaction to the trial medication, unblinding will be undertaken by the sponsor in accordance with the regulatory requirements. Unblinding may also be performed at the request of a senior clinician responsible for the care of a trial participant but such requests are likely to occur only in the case of a serious adverse clinical event and are expected to be rare.

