**Methods and analysis::**

This randomized, double-blind, placebo-controlled, multicenter clinical trial will involve 4 hospitals in Beijing, China. The study will aim to recruit 90 PD patients with constipation between 30 and 80 years-of age with a score of 1 – 4 on the Hoehn and Yahr scale. Once recruited, Patients will be randomized into a BYZJ group or a placebo group in a 2:1 ratio. The trial will include a 1-week run-in period, a 4-week double-blind treatment period, a 4-week and a 12-week follow-up period. All patients will be educated about PD-related constipation during the run-in period. BYZJ granules and simulated granules will be administered twice daily for 4 weeks to the BYZJ group and the placebo group respectively. Assessments will be performed during run-in period, before the start of treatment (baseline, week 0), and at 4, 8, and 16 weeks. The primary outcome will be measured with the Constipation Severity Instrument, and secondary outcomes will be evaluated with the Patient Assessment of Constipation Quality of Life questionnaire, Bristol Stool Form Scale, Movement Disorders–Unified Parkinson Disease Rating Scale, Nonmotor Symptoms Scale, PD Sleep Scale, Parkinson Fatigue Scale-16. Laxative use (dose and frequency) will also be recorded. Intention-to-treat and per-protocol set analyses will be used to compare symptom improvement between the 2 groups. Any adverse events will be recorded.

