## Study design

4

This will be a randomized, double-blind, and placebo-controlled multicenter trial. We aim to recruit 90 patients who will be assigned by stratified randomization (in a 2:1 ratio) to intervention (BYZJ) and control (placebo) groups. The total study duration will be 9 weeks, with a 1-week run-in period, an intervention time of 4 weeks, and 4-week and 12-week washout follow-up periods. Efficacy and safety will be assessed at baseline (week 0) and at 4, 8, and 16 weeks (Fig. 1).

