## Sample size

7

The minimum sample size for statistical significance with a 2-sample 1-sided *t* test was estimated based on the results of a previous study involving the treatment of patients with PD-related constipation.^[13]^ Based on a 2:1 ratio of patients in the BYZJ and placebo groups, the minimum sample size was calculated with formula shown in Eq. (1).: 

In Equation 1, n represents the sample size of each group, κ = nA/nB; μ represents the overall mean, μA represents the mean of group A, μB represents the mean of group B; σ represents the overall standard deviation, σA represents the standard deviation of group A, σB represents the standard deviation of group B; α represents type 1 errors; and β represents type 2 errors. Application of Eq. (1) showed that 52 are required for the BYZJ group and 26 cases are required for the placebo group. Considering a 15% dropout rate, we plan to recruit 60 and 30 cases for the BYZJ and placebo groups, respectively.

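### Section 4 states stratified 2:1 randomization without a factor, but section 8 builds the list by complete randomization without strata, blocks or ratio; the two cannot both be followed

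*Protocol article*

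**What the plan says.** The protocol article describes the allocation method in two places.

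- **Section 4, Study design:** patients will be "assigned by stratified randomization (in a 2:1 ratio) to intervention (BYZJ) and control (placebo) groups". No stratification factor is named.
- **Section 8, Randomization and blinding:** "We plan to use the complete randomization function of SAS 9.13 statistical software". The product is a table of random numbers held in an opaque envelope by a third party. Strata, blocks and the ratio are not mentioned. The two preparations are labelled constipation No. 1 and No. 2.

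Related statements:

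- The abstract says the "multicenter clinical trial will involve 4 hospitals in Beijing, China" and repeats the ratio: "Patients will be randomized into a BYZJ group or a placebo group in a 2:1 ratio".
- Section 7, Sample size: "52 are required for the BYZJ group and 26 cases are required for the placebo group", and then "Considering a 15% dropout rate, we plan to recruit 60 and 30 cases for the BYZJ and placebo groups, respectively".
- Section 16, Statistical analysis, names the independent-samples t-test or a nonparametric test for continuous between-group comparisons and the chi-squared test for counts. It also names a linear mixed model for all continuous variables, without listing its terms. Neither centre nor stratum is mentioned.

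**The concern.** Complete randomization, in its ordinary meaning, is the unstratified, unrestricted scheme. Whoever prepares the list from section 8 departs from section 4, and the reverse. Both sections are current text and nothing in the article reconciles them.

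The allocation list underlies every comparison in the trial and cannot be repaired once patients are enrolled. What is at stake depends on which section is followed, and the two sets of consequences do not add up.

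- **If section 8 is followed,** nothing controls the split between arms within a hospital. On one reading of the phrase, nothing fixes the overall split either.
- **If section 4 is followed,** the simple between-group tests in section 16 do not use the stratification. When the factor is prognostic, their standard errors tend to be too large and the gain from stratifying is lost.

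**Working it through.** **1. The plan's own figures.** Section 7 gives 52 and 26, with 15% dropout. 52 × 1.15 = 59.8 and 26 × 1.15 = 29.9, so 60 and 30 are reproduced. (Dividing by 0.85 would give 62 and 31.) The 52 and 26 themselves cannot be re-derived, because the text gives no values for alpha, power, means or standard deviations.

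**2. Two readings of section 8.**

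- Reading A: each patient is assigned independently, with probability 1/3 of placebo. The placebo count is then Binomial(90, 1/3).
- Reading B: a fixed list of 60 and 30 is put in random order. The overall split is exact; the split within a hospital is hypergeometric.

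Neither reading is stratified.

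**3. Balance within hospitals (both readings).** Assumption: the four hospitals recruit 22, 22, 23 and 23 patients, so about 7 placebo patients are expected in each. Call a hospital unbalanced if it has 4 or fewer, or 11 or more, placebo patients.

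- Reading A: for a hospital of 22, P(≤4) = 0.096 and P(≥11) = 0.079, together 0.175. At least one of four: 1 − (1 − 0.175)^4 = 0.54. Using 22, 22, 23 and 23 gives 0.55.
- Reading B: counting the arrangements of 30 placebo places over 22, 22, 23 and 23 in which every hospital has 5 to 10 gives a probability of 0.642. At least one unbalanced: 1 − 0.642 = 0.358, about 36%.

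**4. Overall split (reading A only).**

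- P(exactly 30 placebo) = 0.089.
- SD = √(90 × 1/3 × 2/3) = 4.5; 95% range 21 to 39.
- P(25 or fewer placebo) = 0.157, before any dropout.

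Fewer than 26 placebo patients does not by itself mean too little precision, because the other arm grows. With information taken as n1·n2/(n1 + n2):

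| Split (BYZJ/placebo) | Information |
|---|---|
| 60/30 (planned) | 20.0 |
| 52/26 (required) | 17.3 |
| 65/25 | 18.1 |
| 67/23 | 17.1 |
| 69/21 | 16.1 |
| 51/39 | 22.1 |

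Information falls below that of 52/26 only at 23 or fewer placebo patients, P = 0.071. The average over all splits is 19.8, about 1% below 20.0.

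**5. Effect on power (reading A only).** Assumption: 80% power at 52/26 with one-sided alpha 0.05, which implies a difference of about 0.60 SD. Power is then 84.8% at 60/30, 77.4% at 69/21 and 87.8% at 51/39. With two-sided 0.05 the figures are 85.3%, 77.0% and 88.6%.

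**6. Analysis.** The t-test, the nonparametric test and the chi-squared test, as named, have no place for a stratum. The mixed model could carry one; the article does not say whether it does.

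**The case against.** The strongest reply is that this is loose terminology. The article fixes 2:1 in the abstract and 60 and 30 in section 7, which fits a shuffled fixed list as well as independent assignment. An article may also leave the stratification factor, block sizes and model covariates to the full protocol or analysis plan.

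Much of that stands, and it rules out four stronger conclusions that a reader might draw.

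- **That the trial cannot deliver 60/30.** Not supported. Under a shuffled fixed list the split is exact, and the figures in steps 4 and 5 fall away. Under independent assignment it is not guaranteed, with little average loss; some chance splits carry more information than 60/30.
- **That section 4 promises stratification by hospital.** It names no factor. Centre is the natural choice with four recruiting hospitals, but that is an inference.
- **That the analysis ignores centre.** This is shown only for the t-test, nonparametric and chi-squared tests. The mixed model's terms may be set out in a plan that is not shown.
- **That chance imbalance between hospitals biases the comparison.** Under unrestricted randomization it costs precision and credibility in a given trial, but it is not bias. Section 13 provides standardized training in the scales for all investigators.

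The reply does not remove the conflict. The point is not that a detail was left out: the article states the method twice, and the statements disagree. That section 8 admits two readings confirms that the method is not fixed.

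One further objection bears on the remedy. The products are identified only as No. 1 and No. 2, so if site staff see the labels, short blocks within a hospital could make coming assignments predictable.

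**Conclusion.** The concern holds in this form: sections 4 and 8 are incompatible, and a list built as section 8 describes would not be stratified. This rests on the text alone.

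The practical size is moderate. The lack of control within hospitals holds on both readings: about a 36% to 54% chance of at least one clearly unbalanced hospital, assuming roughly equal recruitment. The risk to the overall split is conditional on independent assignment: 15.7% for fewer than 26 placebo patients, but only 7.1% for less information than the design requires. The power change at the 69/21 extreme, about 7 to 8 percentage points, rests on assumed alpha and power. The loss from not using the stratum in the simple tests arises only if stratification is carried out, and it cannot be quantified from the article.

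The main reason to act is that the allocation method is undefined, not that power is lost.

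**What to change.** Replace the method sentence in section 8 with one scheme that agrees with section 4:

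- 2:1 randomization stratified by a named factor (centre is the natural choice), and the same factor named in section 4;
- permuted blocks in multiples of 3, of varying size, with the sizes not disclosed to the sites;
- the list generated and held by the third party;
- individual kit numbers in place of the two group labels, so that the blocks do not make allocation predictable.

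In section 16, include the stratification factor as a fixed effect in the primary mixed model for the Constipation Severity Instrument.

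The cost is a different list-generation step, renumbered packaging and one model term. No patients or visits are added and the sample size is unchanged. The list and the numbering can be changed only before enrolment begins, and the article does not give enrolment status. If patients have already been randomized, the article should instead state which method was actually used, and the analysis should follow it.

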## Recruitment, study setting, and participants

5

Participants will be recruited from the PD outpatient clinic of Beijing Rehabilitation Hospital, Capital Medical University, Xiyuan Hospital of China Academy of Chinese Medical Sciences, Dongzhimen Hospital of Beijing University of Chinese Medicine, and Beijing Longfu Hospital. We will also aim to recruit patients through announcements in the media and advertisements that will be published on official information platforms and the bulletin boards of each study site. Interested prospective subjects will be able to contact investigators using the telephone numbers provided. An investigator will conduct a face-to-face interview with each respondent to explain the study. Those who volunteer to participate will be required to sign appropriate consent forms.

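### The packs carry an arm-level label (No. 1 or No. 2), so one disclosed allocation makes every other label decodable by anyone who learns it and can see the packs

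*Protocol article*

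**What the plan says.** Section 8 (Randomization and blinding) sets the order of the two products: "BYZJ granules and BYZJ simulated granules will be provided to patients in the BYZJ and placebo groups, respectively". It then describes the labels: "Both formulations will be provided by the Dongzhimen Hospital pharmacy and labeled as constipation No. 1 and 2, respectively". The packaging safeguard follows: "In order to ensure blinding, both formulations will have identical packaging". The random number table goes to a third party who is not an investigator, and that party also implements the blinding and lifts it after the trial.

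The same section opens two routes to unblinding during the trial. For a suspected unexpected serious adverse reaction, "unblinding will be undertaken by the sponsor in accordance with the regulatory requirements". Separately, "Unblinding may also be performed at the request of a senior clinician responsible for the care of a trial participant"; the protocol expects such requests to be rare.

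Sections 4 and 7 give the scale: 90 participants allocated 2:1, planned as 60 on BYZJ and 30 on placebo. The abstract states that the "multicenter clinical trial will involve 4 hospitals in Beijing, China".

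**The concern.** A blinded label should tell its reader nothing about any other participant. A label with two values, one per arm, shows at a glance which participants share an arm. Only the name of each arm then remains hidden, and a single known allocation supplies both names.

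The stated safeguards protect something else. Identical packaging does not help when the label on it differs by arm. Third-party custody protects the allocation list, but a shared label shows arm membership without the list.

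The outcomes make this matter. In section 12 the primary outcome is the change in the constipation severity score, and most secondary outcomes are symptom or quality-of-life scales. Section 9.1.2 also permits laxatives and records their use. Belief about treatment can move ratings and laxative use in either arm, and none of the analyses in section 16 could restore a blind once lost.

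**Working it through.** The plan states no figure for this point, so there is none to reproduce. The check has three parts.

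**1. What one disclosure decodes**

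- Codes in use: 2, one per arm (section 8).
- Planned participants under those codes: 60 + 30 = 90 (section 7).
- If one participant's label and treatment are both known, that label is decoded, and the other follows by elimination: 2 of 2 labels, covering 90 of 90 planned participants.
- With a unique code per participant, the same disclosure covers 1 of 90.

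The figure of 90 is a maximum. It applies to a person who learns the disclosed allocation and can also see the other participants' labels.

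**2. How likely at least one code break is**

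Let p be the chance that a given participant is individually unblinded. The document does not give p, so the values below are assumptions. Breaks are taken as independent across participants.

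P(at least one break) = 1 − (1 − p)^90

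| Assumed p | (1 − p)^90 | P(at least one break) |
|---|---|---|
| 0.1% | 0.914 | 0.086, about 9% |
| 0.5% | 0.637 | 0.363, about 36% |
| 1% | 0.405 | 0.595, about 60% |

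This is the chance of one or more breaks, not the chance that the trial is unblinded. The two coincide only if the result spreads fully and at once to everyone who sees labels. The column is therefore an upper bound on wider unblinding through code breaks.

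**3. What label counts reveal without any break**

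Suppose a person knows the 2:1 ratio and sees the labels of n participants. That person would guess that the commoner label is active. Treating assignments as independent with probability 2/3 of BYZJ, and taking n odd so that no tie can occur, the guess is right with probability P(X ≥ (n + 1)/2), where X is binomial(n, 2/3):

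| n labels seen | P(commoner label is BYZJ) |
|---|---|
| 9 | 0.855 |
| 23 | 0.952 |
| 45 | 0.990 |

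The value n = 23 is about one site's share if the four hospitals recruit equally (90/4 = 22.5). This is a strong inference for a person who sees a whole site's labels. It is not proof, and a participant who sees only one label cannot make it.

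**The case against.** A reader might infer that a single emergency unblinding, or one correct guess, unblinds every participant at every site. The documents do not support that. Section 8 has the sponsor unblind for a suspected unexpected serious reaction, and nothing says that the result reaches raters, participants or other hospitals. A guess yields a belief, not knowledge. Timing also matters: a break cannot bias ratings already recorded. This objection stands, and it limits the point to what becomes decodable, and by whom.

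A reader might also take 36% or 60% as the chance that the whole trial is unblinded. Those values depend on assumed rates with no basis in the document, which itself expects clinician requests to be rare. At 0.1% the figure is about 9%, and every value assumes full spread. This objection stands too.

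The supplying pharmacy belongs to "Dongzhimen Hospital of Beijing University of Chinese Medicine", which section 5 lists as a recruiting site. It is tempting to count that as a further breach. The article does not say that pharmacy staff recruit, treat or rate participants, and a supplier may know product identity under any coding scheme. It shows no defect in itself.

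The consequences are also partly constrained. Laxative use is tied to three or more days without defecation, which leaves less room for decisions that depend on arm, and no mechanism for differential dropout is documented.

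Finally, the article condenses a fuller protocol, which might add participant kit numbers and a code-break procedure. That lowers confidence that no such code exists. It does not answer the point, which rests on what the article states about the labels and not on an omission. If kit numbers do exist, the sentence on labelling is wrong and needs correcting.

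**Conclusion.** The point holds in limited form. Section 8 states an arm-level label and, alongside it, permits individual unblinding during the trial. One disclosed allocation gives the meaning of both labels and makes up to all 90 planned participants decodable, against 1 of 90 under participant-level codes. That comparison needs only the plain reading of the labelling sentence and does not depend on any code-break rate.

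The probability of a break does depend on assumption: about 9%, 36% and 60% for 0.1%, 0.5% and 1% per participant, as upper bounds on wider unblinding by this route. Inference from label counts under 2:1 allocation is a second and weaker route, open only to someone who sees many labels and knows the ratio.

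The documents do not show that the blind would be lost across the trial. They do show a labelling rule that weakens it needlessly, behind outcomes that are largely subjective ratings.

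**What to change.** In section 8, replace the two group labels with a unique kit or randomization number for each participant, in an order unrelated to arm. Have the third party hold the list that links kit to treatment. Provide individual code breaks, sealed or electronic, so that a sponsor or clinician request reveals that one participant and nothing about the others. Because the article prints the order of the two label numbers, no part of the new label should reuse No. 1 and No. 2 as arm codes. If the full protocol already has participant-level numbers, correct the sentence in the article to say so.

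The cost is minor: relabelling the supplies for 90 planned participants and generating a kit list with the randomization schedule. Sample size, visits, treatment and analysis are unchanged.

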## Intervention

9

### Run-in period

9.1.1

Subjects will receive health education with regards to constipation by specialist personnel during the 1-week run-in period. We also plan to develop a constipation instruction manual that includes dietary guidance, precautions, and the management of bowel habits.

### Treatment period

9.1.2

BYZJ granules (Table 1) consist of *Cistanche*, Chinese wolfberry, *Rehmannia glutinosa*, dogwood, raw *Rehmannia*, *Radix Ginseng*, hemp kernel, raw *Astragalus*, *Gastrodia elata*, and raw licorice (Table 1). Patients will be given BYZJ granules (69.5 g twice daily) dissolved in warm water for 30 to 60 min after both breakfast and dinner (approximately 100–150 mL each time) for 4 weeks.

**Table 1 T1:**
[figure not shown]
Components of the BYZJ formulation.

The placebo will consist of 95% dextrin and 5% BYZJ granules, and will have the same characteristics as and taste as the BYZJ granules. The placebo will be administered at the same dosage and following the same regimen.

If subjects do not defecate for 3 or more days, we will allow them to take a laxative (eg, Kaiseruna) throughout the trial. The amount of laxatives, and the frequency of their use, will be recorded for each patient.

## Conventional anti-Parkinsonian drugs

10

The conventional medical treatment plan used by the subjects will need to meet the requirements of the European Federation of the Neurological Societies guideline for the Treatment of PD.^[14]^ Typical drug types include levodopa, dopamine agonists, monoamine oxidase type B inhibitors, catechol-O-methyl transferase inhibitors, amantadine, and anticholinergics.

## Combined medication

11

Any medication used for comorbidities will be recorded in detail, including the reason for their use, the name of the drug, the dose per administration, the total doses per day, the start date, the date of discontinuation, and the patient's status at the last visit.

## Outcome measures and safety

12

We will collect a range of general information for each patient during the run-in period. The primary and secondary outcomes will be assessed at week 0 (baseline), and then again at weeks 4, 8, and 16. Safety and laboratory indicators will be assessed at week 0 (baseline), and then again at weeks 4 and 16 (Fig. 2). The primary outcome will be the change in constipation severity instrument score. Secondary outcomes include scores for the Patient Assessment of Constipation Quality of Life questionnaire, the Bristol stool form scale, the movement disorders-unified Parkinson disease rating scale, the nonmotor symptoms scale, the Parkinson disease sleep scale, and the Parkinson fatigue scale. We will also record the dose of laxatives and their frequency of use.

